### Sample size

Sample size calculation is based on analyses of covariance (ANCOVA) to compare post-interventions scores of both groups at t_2_ using -t_1_ scores as independent variables. The sample size for the ANCOVA was calculated in a two-step method as proposed by Borm et al. [63]: (1) Calculation of the sample size n as if a t-test on the follow-up scores was carried out, (2) the number of subjects was then multiplied by a “design factor” [(1 – ρ^2^)*n; ρ = correlation between baseline and follow-up scores] to produce the number of subjects required for the ANCOVA.

The calculation is based on data of previous studies [18, 19, 24] with informal caregivers and the following assumptions: (a) An aimed relevant improvement of the CES-D scores of 3 points compared to the control condition (corresponding effect size Cohen’s d of 0.34); (b) depressive symptoms at t_2_ (control: M = 21.0, SD = 10.1; intervention: M = 18.0, SD = 7.6); (c) a correlation ρ = 0.49 between baseline and follow-up measures (the lowest ρ was used); (d) 1- β = .80 (power); and (e) α = .05 for a two-sided t test, (f) a ratio of n (control) / n (intervention) = 1.00. (1) Using a formula for a two-sample t-test (G*Power Vs. 3.1.9.2) [64] the required total sample size is 282. (2) The required adjusted sample size for ANCOVA with the same power as the t-test is 216 [design factor: (1- 0.49^2^)*n (total)].

Possible different strategies to promote study participation of the two participating insurances are an element of uncertainty in the sample size calculation. Therefore, we added an additional 10% to the calculated 216 participants to compensate a possible shift in variance. Taking this into account, the aimed sample size is 238.

Based on the same assumptions (two-sided t-test, α = .05, 1- β = .80, d = .34) and data of our previous work, the correlations between baseline and follow-up measures of secondary outcomes are expected to be ρ = .40 (VAS Mood), ρ = 0.72 (GBB-24), 0.59 (SPSI-R:S / Subscale “Negative problem orientation”), and ρ = 0.70 (SCQ-AB / Subscale “satisfaction with one’s own performance”). Because of these higher correlations in comparison to the CES-D we assumed that the total sample size of 216 participants will be sufficient to detect at least moderate effects in all secondary outcome measures except the ‘VAS Mood’. For this scale, the aimed sample size of 238 is still sufficient. 

Based on our previous studies we assumed dropout rates of 15% between -t_1_ and t_1_ and 20% in each of the following two 6-month intervals (t_1_ to t_2_, t_2_ to t_3_). Based on these assumptions we aim to enrol 572 caregivers. The participant flow and numbers through the study are summarized in Fig. 2.

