### Protocol amendments

Because dropout rates have been lower than expected in this ongoing study, the aimed recruitment number has been reduced from 572 to 504 to achieve the planned study completer sample of 238 caregivers. In line with the changing actual national and local COVID-19 restrictions and official instructions of the participating long-term care insurances (restricted home visits), the following alternative settings for the initial home visit in *setting a* of intervention 1 are allowed: face-to-face contact in the service centre of the long-term care insurance or telephone-based initial contact. These possible setting variations because of actual restrictions will be considered in the data analyses.

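### The aimed sample of 238, the printed 15%/20%/20% dropout and the enrolment target of 572 do not reconcile, and the amended 504 carries the mismatch forward

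*Protocol article*

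**What the plan says.** All references are to the protocol article.

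- **Sample size, basis.** "Sample size calculation is based on analyses of covariance (ANCOVA) to compare post-interventions scores of both groups at t_2", with the baseline score as covariate. The Abstract also makes t2 (9 months) the primary endpoint.
- **Sample size, steps.** The inputs are a 3-point CES-D difference, t2 values of "control: M = 21.0, SD = 10.1; intervention: M = 18.0, SD = 7.6", a correlation of 0.49, 80% power and "α = .05 for a two-sided t test". They lead to 282 for the t-test, 216 after the ANCOVA design factor, and 238 after a 10% addition.
- **Sample size, dropout.** "we assumed dropout rates of 15% between -t_1_ and t_1_ and 20% in each of the following two 6-month intervals". The next sentence reads: "Based on these assumptions we aim to enrol 572 caregivers". For the flow of participants it refers to Fig. 2.
- **Protocol amendments.** Because fewer caregivers were lost than foreseen, "the aimed recruitment number has been reduced from 572 to 504 to achieve the planned study completer sample of 238 caregivers".

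**The concern.** Required sample, dropout and enrolment form one chain, and the article says explicitly that 572 rests on the dropout rates just given. Applied to 238, those rates give a much smaller number for either follow-up visit. The amendment then describes dropout as better than assumed, but its own pair of numbers implies heavier loss than the printed rates.

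Two things are at stake. First, recruitment was reduced during the trial on a justification that the printed figures do not support. Second, the expected share of missing primary outcomes depends on which figure is wrong. It is 32% at t2 with the printed rates, but 40.5% if the later intervals were planned at 30% loss. That matters because the intention-to-treat analysis (Statistical methods) fills missing values by multiple imputation.

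**Working it through.** **1. The plan's own steps up to 238 reproduce.**
- Pooled SD = √((10.1² + 7.6²)/2) = 8.94, so d = 3/8.94 = 0.336 (printed as 0.34).
- Two-sample t-test, two-sided 5%, 80% power, unrounded d: 140.3, so 141 per arm and 282 in total.
- Design factor 1 − 0.49² = 0.7599. 141 × 0.7599 = 107.1, so 108 per arm and 216 in total.
- 216 × 1.10 = 237.6, so 238.

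**2. The step from 238 to 572 does not.**
- Retention at t2: 0.85 × 0.80 = 0.680. Enrolment needed: 238/0.680 = 350.
- Retention at t3: 0.85 × 0.80 × 0.80 = 0.544. Enrolment needed: 238/0.544 = 437.5, so 438.
- Adding the rates instead of compounding them: 238/0.65 = 366.2, so 367 (t2); 238/0.45 = 528.9, so 529 (t3).
- Multiplying up by (1 + rate): 238 × 1.15 × 1.20 = 328 (t2); × 1.20 again = 394 (t3).

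None of these gives 572. In the other direction, 238/572 = 41.6%, a loss of 58.4%, against printed losses of 32.0% by t2 and 45.6% by t3.

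**3. Two unstated routes do give 572.**

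| Route | Base | Loss per interval | Calculation | Flow from 572 (t1, t2, t3) |
|---|---|---|---|---|
| A | 238 | 15%/30%/30% | 238/(0.85 × 0.70 × 0.70) = 571.4 | 486, 340, 238 |
| B | 282 × 1.10 = 310.2, so 311 | 15%/20%/20% | 311/0.544 = 571.7 | 486, 389, 311 |

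If A was used, the printed dropout rates are wrong. If B was used, the ANCOVA reduction was left out of the enrolment step, and 238 is not the base of 572.

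**4. The amended target.**
- 238/504 = 47.2%, a loss of 52.8%. This exceeds the printed 45.6% through t3.
- It is below the 58.4% implied by the pair 572 and 238.
- With 15% loss in the first interval, 504 to 238 needs 1 − √(0.4722/0.85) = 25.5% in each later interval, against 20% printed.

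**5. Power.** The normal approximation is Φ(3/(8.94 × √0.7599 × √(2/n)) − 1.96), with n per arm. It assumes that the correlation of 0.49 also holds at t3.

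| Total analysed | Where it comes from | Power |
|---|---|---|
| 216 | ANCOVA requirement | about 81% |
| 238 | aimed sample | about 84% |
| 389 | 572 × 0.680, t2 | about 97% |
| 343 | 504 × 0.680, t2 | 94% to 95% |
| 311 | 572 × 0.544, t3 | about 92% |
| 274 | 504 × 0.544, t3 | about 89% |

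Under route A, t2 would have 572 × 0.595 = 340 or 504 × 0.595 = 300 caregivers, with power of about 94% or 92%.

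**The case against.** Four arguments limit the point.

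- **Fig. 2.** Its caption says that it gives planned numbers per stage, and it was not available for this check. A reader who has it may see at once which route was used. That stands, so one cannot say that the error is untraceable. But the figure cannot make the sentence true that derives 572 from the printed rates.
- **Other losses.** The Participant timeline section excludes data collected after caregiving has ended from the main outcome analysis. This could bring the analysable number below questionnaire retention. The Sample size section does not include such a loss in the calculation, so it is only a possible explanation.
- **The amendment.** The article does not claim to derive 504 from 15%/20%/20%; it cites experience in the running trial. Measured against the 58.4% implied by 572 and 238, a loss of 52.8% is indeed lower. So 504 is the same discrepancy carried forward, not a second, independent error.
- **Consequences.** Every reading examined leaves more than 238 caregivers at t2. Neither the primary test nor what it estimates changes.

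A reader might go further and infer that 30% loss must have been used. Route B gives 572 equally well with the printed rates, so the text does not settle this. A reader might also infer that enrolment was deliberately sized for t3. The dropout listed through t3, the reference to completers and both routes point that way, but no sentence says so, and at the printed rates 572 exceeds the t3 need by 572 − 438 = 134. Sizing for t3 would not be an error in any case, since a number sufficient there is sufficient at t2.

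**Conclusion.** The point holds as a mismatch of printed figures: 238, 15%/20%/20% and 572 cannot all be right. At the printed rates, 572 exceeds the need by 222 (t2) or 134 (t3), and 504 exceeds it by 154 or 66. The amendment's reason conflicts with the printed rates, because 504 to 238 implies 52.8% loss against 45.6%.

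This is not a finding of lost power, although a reader might take it as one. The 80% at 216 is correctly computed, and under the plan's assumptions (3 points, the stated SDs, correlation 0.49) power at t2 is above 80% on every reading. If the printed rates are right, the issue is enrolment beyond what the primary question needs. If they are not, it is an understated expectation of missing outcomes. Which applies cannot be decided from the text.

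The figures should be corrected, because enrolment and its mid-trial reduction both rest on them. The matter does not endanger the primary analysis.

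**What to change.** 1. In Sample size, state the base number, the dropout rate per interval and the time point actually used, so that they reproduce 572 and agree with Fig. 2. Alternatively, correct the figure that is wrong.
2. Give the expected number and the power at t2, the primary time point, separately from t3.
3. In Protocol amendments, report the dropout observed per interval when the decision was taken, say at which visit the 238 completers are counted, and re-derive 504 from those figures.

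The cost is restated figures and a few sentences. No extra participants and no change to the analysis are needed.

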### Recruitment

Recruitment including a short screening for caregiver burden (eligibility criteria h) is carried out by employees of two participating German long-term care insurances (AOK Baden-Württemberg, AOK Bavaria). These two insurances have together 8.4 million members with more than 350,000 of them being dependent on care. Different recruitment strategies are planned to get access to the target group [e.g., caregivers of care recipients after an increase of the care degree (§18 SGB XI), mandatory counselling (§37.3 SGB XI), contacting insurance members via phone, letters and other forms of advertising]. The planned strategies are coordinated with the administration and data protection officials of the insurances. Each of the two participating insurances is planned to recruit 50% (*N* = 286) of the aimed total number of participants. Employees of the insurances inform caregivers about the study, administer the short screening (eligibility criteria “h”) to identify distressed caregivers, and ask for the consent to forward the caregiver contact details to the study team of the University of Jena. A member of the study team informs about further details of the study (via phone and written information) to enable the caregiver to make an informed decision whether to participate in the study or not. Participants have to agree to written and audiotaped (only intervention 2) records of the sessions, trial-related audits, readout of health care cost-data if being a member of one of the two participating insurances (2 years before -t_1_ until t_3_), and data processing and analyses within the study. The signed consent form has to be sent in a prepaid reply envelope to the study team of the University of Jena before enrolment.

### Allocation

After baseline assessment (-t_1_) caregivers are randomly assigned (t_0_) to one of two groups (intervention or usual care control group). Concealed randomization sequence is performed in permuting blocks with different block sizes. The allocation ratio is 1:1. Randomization is stratified for region respective insurance (AOK Bavaria, AOK Baden-Württemberg with a 1:1 ratio) and for sex (male, female with 1:4 ratio). The computer-generated randomization lists have been generated by an independent randomization unit at the University of Ulm. After receiving a new ID number including sex and state via E-Mail from the study team of the University of Jena, the allocation is performed and mailed back by a study assistant from the University of Ulm not involved in the recruitment processes and without any participant contacts.

### Blinding

In accordance with the requirements of the data protection guidelines of the two insurances, the scientific partners and the ministries of social affairs of the two states, study participants have to be informed about the different possible study arms and interventions before enrolment. Therefore, participating caregivers are not blinded. Counsellors of the insurances and the psychotherapists delivering the interventions are informed that they provide an intervention within the ReDiCare study. Participants should complete questionnaires themselves. When the blinded assessors are trying to clarify open questions and checking the completeness of the questionnaires in a phone call, participants can reveal their intervention. Data analysts of the University of Ulm are blinded to the allocation status.

### Data collection methods

For assessments, the evaluation team (psychologists) send the questionnaires with individual code numbers by post to the caregivers who are asked to answer the questions. In a following phone contact the questionnaire is reviewed for completeness and unclear points are discussed. After this telephone contact, the questionnaires should be returned in a return envelope. This survey technique with an additional phone call is used because a mostly elderly study population is expected and, in particular, the questions on the used health services are often not easily answered. Furthermore, the acceptance of the survey is to be improved and the risk of missing data or dropouts to be reduced.

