### Intervention

Caregivers in the intervention group receive in a stepped approach a low-threshold care counselling first (intervention 1). Intervention 2 is offered depending on the counsellor’s evaluation (caregiver coping with the caregiving situation) and recommendation or, alternatively, a positive caregiver self-assessment (depressive symptoms, difficulties in coping with the caregiving situation) after t_1_. 

From the perspective of a prevalent caregiver stress-process model [29] we want to support caregiver resources and coping strategies with our intervention. Previous research could show that positive gains can coexist with stressful occurrences [30] and that benefit-finding through cognitive reappraisal can reduce depressive symptoms [31]. Therefore, we expanded Pearlin’s stress model [29] by positive aspects of caregiving (Fig. 1). We assume that increased positive emotions as outcome will in turn help to restore resources and sustain different forms of coping [32]. In line with the national care counselling guidelines [17] we address in intervention 1 mainly everyday problems and unmet practical needs of caregivers that are causing distress. The optional and more intense intervention 2 expands the focus on psychological aspects like the appraisal of the caregiving situation, emotional distress regulation (emotion-focused coping) and positive gains despite hardship (meaning-focused coping).

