#### Satisfaction of patients and interventionists with the intervention

A set of questions is used to assess the satisfaction of caregivers with intervention 1 at t_1_, and with intervention 2 at t_2_. Six questions cover the general setup of the intervention (setting, number of sessions, and duration of a single session) and perceptions of helpful and unhelpful aspects of the intervention, further 24 items the competence and experience with the counsellor and therapist. In addition, three items of the Client Satisfaction Questionnaire (CSQ-8) [57] focus on the quality of service, and general satisfaction of the participant. After the follow-up (t_3_) the participants are asked to comment on the intervention on ten different aspects (ratings and open questions) from a retrospective perspective. In addition to the caregivers, all care counsellors in intervention 1 are asked for feedback (ratings and open questions) on their experience with the intervention approach (materials, feasibility, etc.), the training, supervision and supervisors after the initial training, the middle and end of the intervention period.

In intervention 2 Goal Attainment Scaling (GAS) [58] is used to evaluate participants’ personal goal attainment. During the first and/or second telephone sessions, the caregiver and the therapist identify the caregiver’s personal goals for the intervention 2. The steps of GAS are formulating goals, describing goals in observable terms, defining a hierarchy of goals and potential outcomes. In the last therapy session, therapists and caregivers rate the goal attainment.

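### The assessment call discusses the questionnaire before it is returned and nothing exempts the CES-D, so primary-outcome answers stay open to change with a caller who may know the arm

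*Protocol article*

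**What the plan says.** Data collection methods fixes a sequence. Psychologists of the evaluation team post the questionnaires. Then "In a following phone contact the questionnaire is reviewed for completeness and unclear points are discussed". Only then does the form leave the caregiver: "After this telephone contact, the questionnaires should be returned in a return envelope". The reasons given are a mostly elderly sample, better acceptance, fewer missing data and dropouts, and that "in particular, the questions on the used health services are often not easily answered".

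The Blinding section says "Participants should complete questionnaires themselves" and calls the callers blinded, but adds that when they are clarifying open questions and "checking the completeness of the questionnaires in a phone call, participants can reveal their intervention". The Discussion repeats this as a limitation: it calls assessor blinding questionable and names the same telephone check as the route.

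The section on satisfaction states: "A set of questions is used to assess the satisfaction of caregivers with intervention 1 at t_1_, and with intervention 2 at t_2" (the 9-month visit). The CES-D at that visit is the primary outcome.

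**The concern.** Participants in this trial cannot be blinded, and the CES-D is self-reported. That part of the measurement bias is unavoidable and is acknowledged. The call adds a separate influence that could be avoided. A psychologist goes through the questionnaire with the caregiver while the form is still in the caregiver's hands. If that psychologist has learned the arm, the way an unclear item is explained can differ by arm, and the caregiver can act on the explanation before posting the form.

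The plan treats disclosure as a threat to blinding and stops there. It does not say that the primary outcome is settled before the moment at which disclosure is expected, or that the discussion stays away from symptom items. At stake is a between-arm shift in the CES-D that no analysis could separate from a treatment effect.

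**Working it through.** The point is about procedure, so most of the check sets the sections side by side.

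1. **Is the CES-D within the call?** Data collection methods describes the procedure for assessments in general and for the questionnaire as a whole. Neither that section, nor Blinding, nor the section on the primary outcome measure takes the CES-D out of it. So it is within the call as written.

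2. **Can answers still change?** The order is post, call, return. The caregiver holds the form during and after the call. Nothing bars a change to an answer already given.

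3. **Is disclosure in the call likely?** Two routes:
   - *Service use.* The call is justified especially by the health-service questions, in a trial that delivers counselling and, for some, psychotherapy by telephone. Routine counselling is also open to controls, so mention of counselling alone would not settle the arm. An account of the study's own contacts would. This route does not depend on how the forms are bundled.
   - *Satisfaction items.* The article describes 6 + 24 + 3 = 33 items. Controls have no study intervention to rate. The 3-month items concern intervention 1. The 9-month items concern intervention 2, which is optional, so they apply only to those who received it. The article gives the time points but not whether these items share a form, a mailing or a call with the outcomes. Table 3 is not shown.

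4. **Do the stated reasons need this scope?** Reducing missing data does require a check that CES-D items are filled in. It does not require discussing what they mean or reopening answers already given. The difficulty with health-service questions does not concern the CES-D at all.

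5. **A yardstick, not an estimate.** The documents give no size for this bias. What can be computed is how sensitive the primary test would be to a shift of an assumed size. Inputs from the Sample size section: difference 3 points; SDs 10.1 and 7.6; correlation 0.49; two-sided 5%; N = 238.
   - Pooled SD = √((10.1² + 7.6²)/2) = 8.94, so d = 3/8.94 = 0.336. The t-test then needs 282 in total, as stated.
   - 282 × (1 − 0.49²) = 214.3 (stated: 216). Then 216 × 1.1 = 237.6, i.e. 238, as stated. The small gap between 214.3 and 216 has no bearing here.
   - Residual SD = 8.94 × √(1 − 0.49²) = 7.79. Standard error of the arm contrast = 7.79 × √(4/238) = 1.01 points.
   - With no true effect and an assumed artefactual shift b, the rejection rate is 1 − Φ(1.96 − b/1.01) + Φ(−1.96 − b/1.01):

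| Assumed shift b (CES-D points) | Two-sided rejection rate |
|---|---|
| 0 | 5% |
| 0.5 | 8% |
| 1.0 | 17% |
| 1.5 | 32% |
| 2.0 | 51% |

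The values of b are assumptions without a source in the document. The table shows only that small shifts are not harmless when the target is 3 points.

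**The case against.** The strongest reply is that the authors have already said this. The Discussion concedes that assessor blinding is questionable and names the telephone check as the cause. That stands: the plan did not overlook the risk, and anyone who infers that it did is wrong. But a stated limitation is not a safeguard, and neither section notes that the primary-outcome form is still open at that point.

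Three stronger readings are tempting, and the documents do not support them.

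- A reader might infer that the satisfaction items reveal the arm to the caller as a matter of course. The article does not place them in the reviewed form. Separate collection may already be the practice, and at 9 months they concern only those who received intervention 2. The self-assessment used for stepping up is dated after the 3-month visit and is not said to pass through the evaluation team, so it adds nothing.
- A reader might infer that CES-D answers are in fact revised with an unblinded assessor. No section says so. Participants are meant to complete the forms themselves, and the review is described as one for completeness.
- A reader might infer that a caller who learns the arm at 3 months carries it to the primary assessment. The article does not say whether the same person calls again.

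It can also be said that call scripts and disclosure logs belong in a fuller protocol or a monitoring plan. That is fair for the scripts. The order of call and return, however, is stated here, for the whole questionnaire, and it is the order that leaves the CES-D open.

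**Conclusion.** The point holds in a limited form. As written, the whole questionnaire, CES-D included, is reviewed and its unclear points are discussed before it is returned, so primary-outcome answers can be changed during a call with an assessor who may have learned the arm. Disclosure is likely from the service-use discussion alone, and more likely if satisfaction items sit in the same form.

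The size of any bias, and hence its effect on the trial's result, cannot be estimated from the document. Since participants know their arm and rate themselves, protecting the CES-D from the caller removes only part of the measurement bias. It is the part that can be removed at almost no cost.

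**What to change.** - Instruct caregivers to complete the CES-D and the other symptom scales before the call.
- For these scales, limit the call to a scripted prompt that an item is blank, with no discussion of content and no change to answers already given. Keep open discussion for health-service and cost items.
- Take the service-use items last in the call, and collect satisfaction items after the outcome form is back.
- Have callers log any disclosure of the arm and any CES-D item completed during the call.
- In the Blinding section, describe the assessors as initially blinded, with disclosure logged.

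Sealing or posting the CES-D before the call would protect it further, but it would rule out the prompt for blank items and give up some completeness, so it is not the first choice.

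The cost is a small change in mailing or call order, a short script, and possibly a few more unclear or blank CES-D items. Because Protocol amendments describes the trial as ongoing, the date of the change should be recorded so that assessments before and after it can be told apart.
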